## Abstract

Research on the use of Acceptance and Commitment Therapy (ACT) for patients with degenerative lumbar pathology awaiting surgery are limited. However, there is evidence to suggest that this psychological therapy may be effective in improving pain interference, anxiety, depression, and quality of life. This is the protocol for a randomized controlled trial (RCT) to evaluate the effectiveness of ACT compared to treatment as usual (TAU) for people with degenerative lumbar pathology who are candidates for surgery in the short term. A total of 102 patients with degenerative lumbar spine pathology will be randomly assigned to TAU (control group) or ACT + TAU (intervention group). Participants will be assessed after treatment and at 3-, 6-, and 12-month follow-ups. The primary outcome will be the mean change from baseline on the Brief Pain Inventory (pain interference). Secondary outcomes will include changes in pain intensity, anxiety, depression, pain catastrophizing, fear of movement, quality of life, disability due to low back pain (LBP), pain acceptance, and psychological inflexibility. Linear mixed models will be used to analyze the data. Additionally, effect sizes and number needed to treat (NNT) will be calculated. We posit that ACT may be used to help patients cope with the stress and uncertainty associated with their condition and the surgery itself.

## 1. Introduction

Chronic pain is considered a multidimensional experience, and it is accepted that both the intensity and the characteristics of pain are influenced by the individual’s cognitive processing [1]. Chronic pain involves a high comorbidity with mental disorders and the presence of clinically relevant psychopathology [2,3]. There is evidence of the effectiveness of Acceptance and Commitment Therapy (ACT) in patients with chronic pain, both in individual and group formats [4,5,6,7,8,9].

Specifically, ACT maintains that language is at the base of psychological problems, making it inevitable that under certain conditions thoughts and sensations arise that can be experienced as annoying. The fact of being verbal also makes it easier for people to become entangled in fighting against their own private events, and to persist in them even though the results of such struggles are often counterproductive. Using metaphors, paradoxes, and experiential exercises, people learn to be in touch with thoughts, feelings, memories, and sensations, both those previously feared and avoided and any others that arise. In this way, people learn the ability to recontextualize these private events, clarify what matters to them in their lives—what deep down and radically they value—and gain commitment to the necessary changes in the action [10,11].

Low back pain (LBP) is a problem that affects around 11 to 84% of the general population at some point in their lives [12,13]. There are several environmental and personal factors that influence the onset and course of LBP, including comorbid anxiety and depression, as well as certain types of cognitive variables, such as pain catastrophizing [14]. Particularly, pain catastrophizing is one of the psychological constructs that has been most researched in relation to pathologies that cause pain. It is defined as a set of cognitive and emotional processes that predispose pain to become chronic. Individuals who catastrophize develop a very negative view of their pain, think about it often, and feel unable to control it, so they have a worse prognosis for any treatment [15]. Therefore, early detection of risk factors for LBP has been identified as a strategy for identifying patients who may be at risk of poor clinical outcomes, and as a potential method for improving the effectiveness and cost-effectiveness of psychological therapies [16].

Degenerative low back conditions, such as spinal stenosis and facet arthrosis, lead to chronic pain, impairment, and reduced quality of life [17]. The prevalence in the general population varies from 20% to 25% and increases to over 45% in people over 60 years of age [18,19,20]. Lumbar spinal stenosis is one of the most common diagnoses associated with spinal surgery [21,22]. Surgical treatment for lumbar degenerative conditions is well established and studies have reported that the benefits of surgery are maintained in the long term, although there are hardly any studies that compare it with other types of treatments such as pharmacological ones [23]. Despite advances in surgery, after lumbar spine surgery, adults continue to have poorer physical conditions and mental health outcomes compared to the general population [24,25]. Studies have found persistence of pain, functional disability, and poor quality of life in up to 40% of people after spinal surgery for lumbar degenerative conditions [26,27,28,29]. The reoperation rate has been reported to range from 18% to 23% between 8 and 10 years after surgery [30]. Even though there are logical benefits of surgical treatments, there is also a risk that the patient develops so-called chronic postsurgical pain (CPSP), the incidence of which varies depending on the type of operation between 5% and 85% [31].

According to the International Association for the Study of Pain (IASP), CPSP is defined as chronic pain that develops or increases in intensity after a surgical procedure and is categorized as secondary chronic pain [32]. Although the risk factors for CPSP are common with other types of chronic pain, current evidence has established that the factor most associated with this pathology is the duration of intense acute postoperative pain [33]. This kind of pain can generate central sensitization, which lowers the mechanical threshold and exaggerates the response to noxious stimuli. Therefore, the patient may present with both hyperalgesia and allodynia. Reports indicate that between 10% and 70% of patients requiring major surgery go on to develop CPSP depending on the type of surgery (e.g., cardiac, thoracic, gynecologic, and spinal) [34]. A recent meta-analysis [35] found an association between anxiety, catastrophizing, depression, kinesiophobia, and CPSP. People with chronic degenerative LBP who are candidates for surgery, with higher rates of catastrophizing, anxiety, depression, and fear of movement (kinesiophobia), will have a higher risk of pain chronification and worse prognosis in relation to the efficacy of surgical treatment.

The first step in addressing this type of pain, as well as the disability and suffering it entails, is to identify the modifiable and protective causal risk factors that predict the CPSP. The identification of psychological risk and protective factors for CPSP will serve for the development and implementation of psychological interventions to prevent and/or manage CPSP [35]. Expanding knowledge of the psychological and social predictors of CPSP is essential to recognize patients at risk of poor outcomes. As psychological risk factors for CPSP, anxiety (both as a state and as a trait), depression, catastrophizing, and kinesiophobia have a significant association with chronic postoperative pain. Of the psychological predictors that have a significant association with chronic postoperative pain, the state of anxiety is the most explanatory. Anxiety is understood as an emotional reaction or as a personality trait [35,36]. Trait anxiety refers to the individual tendency to react anxiously, while the state is described as a transient emotional state that fluctuates over time. Kinesiophobia, defined as “an excessive, irrational, and debilitating fear of physical movement and activity resulting from a feeling of vulnerability due to painful injury or reinjury” is found to be a central factor in the process of pain developing from acute to chronic stages [36].

There is a growing understanding of the important role that psychological interventions can play in reducing negative affect, avoidance behaviors, and pain perception after surgery. Specifically, ACT allows patients to learn to expand their ability to experience and accept pain, including the negative thoughts and feelings that inevitably arise when pain is present. Physical pain sensations, as well as patient psychological reactions to them, are observed in a neutral, non-reactive manner, while focusing on improving motivation and commitment to engage in personally meaningful, achievable, and goal-oriented activities. This is practiced without engaging in problematic avoidance behaviors, which typically worsen pain and limit functioning. Patients become more psychologically flexible and learn to adapt their behavior in a way that allows them to live a rich and meaningful life [37]. Finally, previous studies have shown that psychological predictors have a significant association with the development of CPSP. Kinesiophobia and depression are independently associated with chronic postsurgical pain and disability and decreased physical function after lumbar spine surgery [38,39,40,41,42,43,44].

The present work describes the design of a randomized controlled trial (RCT) comparing the effectiveness of preoperative ACT versus treatment as usual (TAU) to improve pain interference in patients subjected to surgery for degenerative lumbar pathology. Considering the above evidence, we hypothesize that participants who engage in ACT will have greater improvement in quality of life and less disability and pain interference compared to participants who do not engage in ACT. The objectives of this RCT are the following: (a) to analyze the effectiveness of ACT as an adjuvant to TAU to improve pain interference (primary outcome); (b) to examine the effectiveness of ACT for improving pain intensity, anxiety, depression, pain intensity, quality of life, functional status, kinesiophobia, pain catastrophizing, psychological flexibility, and pain acceptance (secondary outcomes); and (c) to explore the differences between responders and non-responders in terms of sociodemographic and clinical characteristics.

## 2. Materials and Methods

### 2.1. Design

This study is a 12-month RCT that follows the guidelines of the Standard Protocol Items: Recommendations for Interventional Trials (SPIRIT) [45] and the Consolidated Standards of Reporting Trials (CONSORT) [46]. The study has two treatment arms: a control group that receives TAU and an intervention group that receives TAU + ACT. The study is registered on ClinicalTrials.gov, accessed on 5 December 2022, with the NCT number NCT05634122. Patients in both arms will receive TAU as it is commonly provided by the Spanish National Health System [47].

### 2.2. Participants and Sample Size

The sample size was estimated through R with R Studio using the package “pwr.t.test” version 4.3.0. This sample size was determined to achieve a power of 80%, a significance level of 5%, and a treatment effect size based on Cohen’s *d* of 0.64 and 0.73 for pain interference (BDI) at post-treatment and at follow-up, respectively [48]. Considering a dropout rate of 30% [48,49,50,51], it will be necessary to include 51 subjects in each study arm. A total of 102 patients with degenerative lumbar pathology who are candidates for lumbar surgery from the Spine Unit of Hospital del Mar (Barcelona, Spain) will be recruited for this study.

Patients who have been scheduled for surgery in the Spine Unit and who have been diagnosed with degenerative pathology that also present psychosocial risk factors for CPSP, as determined by screening questionnaires, will be assessed by the Pain Unit psychiatrist starting June 2023 and will be recruited if they meet the selection criteria. Inclusion criteria will be (a) age 18–80 years, (b) adequate understanding of Spanish or Catalan, (c) meeting the diagnostic criteria for the LBP/degenerative low back pathology that indicates a candidate for first surgical treatment according to the clinical history (International Classification of Diseases [ICD]-10 codes for surgical and diagnostic processes) [52], (d) presence of psychosocial risk factors for CPSP, (e) having an internet connection on a smartphone, tablet, or computer to be able to participate in online therapy, and (f) giving authorization by signing informed consent. Specifically, the psychosocial risk factors associated with CPSP are anxiety, depression, catastrophizing, and fear of movement [35,36]. During the outpatient visit to the Spine Unit, and once the surgical intervention has been proposed and accepted by the patient, the patient will complete three self-administered questionnaires: The Hospital Anxiety and Depression Scale (HADS), Pain Catastrophism Scale (PCS), and Tampa Scale of Kinesiophobia (TSK-11). To select the participants, the cut-off points are high in relation to the HADS (cut-off point ≥ 11), PCS (cut-off point ≥ 24), and TSK-11 (cut-off point ≥ 27), which are based on what was suggested by the authors and reviewers of the adaptations of each questionnaire [53,54,55].

Exclusion criteria will be (a) cognitive impairment (understood as a decline in a person’s cognitive abilities, such as memory, attention, language, and reasoning,) that, in the clinician’s opinion, prevents them from participating in therapy, (b) presence of chronic pain not related to the diagnosis of LBP that indicates a candidate for surgical treatment, (c) not presenting psychosocial risk factors for CPSP, (d) being involved in litigation or pending legal claims for compensation, (e) having a severe or decompensated psychiatric disorder (such as severe depression, schizophrenia, bipolar disorder, or personality disorder) that, in the clinician’s opinion, prevents participation in therapy, (f) suicidal ideation, (g) consumption of toxic substances in abuse/dependence, except for smoking, and (h) having a surgical indication for lumbar surgery that involves reintervention.

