### 2.6. Statistical Analysis

Data analyses will be carried out using the statistical packages SPSS v26.0, R with R Studio v4.0.2, and MPlus v7.4. Comparative analyses of continuous data will be performed using the Student’s *t* test or their non-parametric equivalents (i.e., Mann–Whitney U or Kruskal–Wallis test), depending on the characteristics inherent to the variables under study. The Chi-Square test or Fisher’s exact test will be used, as appropriate, for categorical variables. The Bonferroni correction will be applied in all post hoc tests. In all statistical tests performed with the outcome variables, a statistical significance level of 0.05 will be used. In adherence with CONSORT recommendations, potential baseline differences in sociodemographic and clinical characteristics are considered irrelevant after randomization and, as a result, were not included as covariates in the analyses of RCT outcomes.

The main analysis will compare the effect ACT compared to TAU on the primary outcome (pain intensity and pain interference at 12-month follow-ups). All data analyses will be carried out following an intention-to-treat (ITT) principle, that is, regardless of protocol adherence. Then, we will compute analysis of the primary outcome post-treatment and analysis of the secondary and treatment process outcomes at post-treatment and at 12-month follow-up. The analyses will be replicated from a per-protocol approach. Multi-level, linear mixed models will be created using the restricted maximum likelihood method for the estimation of parameters. The effect sizes will be calculated according to Cohen’s *d*. A 5% significance level will be used in all 2-tailed tests, applying the Benjamini–Hochberg correction for multiple comparisons (to reduce the risk of false positives).

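### With 51 per arm and the stated 30% dropout, power at the post-treatment effect (d = 0.64) is about 76%, not 80%; the follow-up effect (d = 0.73) keeps about 86%

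*Protocol article*

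**What the plan says.** Section 2.2 (Participants and Sample Size) names the tool: "The sample size was estimated through R with R Studio using the package “pwr.t.test” version 4.3.0". That function gives power for t tests. The target is 80% power at a 5% significance level, and the effects are "Cohen’s *d* of 0.64 and 0.73 for pain interference (BDI) at post-treatment and at follow-up, respectively". The paragraph then ends: "Considering a dropout rate of 30% [48,49,50,51], it will be necessary to include 51 subjects in each study arm". The Abstract repeats the total: "A total of 102 patients with degenerative lumbar spine pathology will be randomly assigned".

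Section 2.6 (Statistical Analysis) settles the sidedness: "A 5% significance level will be used in all 2-tailed tests". It places the main analysis at 12 months and the post-treatment analysis of the primary outcome after it.

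Section 2.2 prints neither the number of completers required before dropout nor the formula used to allow for dropout. It gives one dropout rate and does not tie it to a visit.

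**The concern.** The paragraph reads as a claim that 51 per arm gives 80% power for both effects after 30% are lost. If *n* completers are needed and 30% of those enrolled are lost, enrolment must be *n*/0.7. Multiplying *n* by 1.3 falls short, because 1.3 × 0.7 = 0.91 and only 91% of the required completers remain. The stated 51 fits the multiplication and not the division.

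What is at stake is the accuracy of a stated design property. A reader of a null post-treatment result would take the trial to have had 80% power under its own dropout assumption, when the paragraph's inputs give somewhat less.

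**Working it through.** **Inputs.** From section 2.2: two-sample t test, power 80%, alpha 5%, d = 0.64 and d = 0.73, dropout 30%, 51 per arm. From section 2.6: two-sided tests.

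**Method.** With *n* completers per arm, the t statistic has 2*n* − 2 degrees of freedom and noncentrality d × √(*n*/2). Power is the probability that it exceeds the two-sided 5% critical value.

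**1. Completers needed for 80% power.**
- d = 0.64: *n* = 39.31, rounded up to 40 (39 by the normal approximation).
- d = 0.73: *n* = 30.45, rounded up to 31.

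**2. Reproducing the stated 51.**

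| Basis (two-sided) | × 1.3 | ÷ 0.7 |
|---|---|---|
| d = 0.64, *n* = 39.31 | 51.1 | 56.2, so 57 |
| d = 0.64, *n* = 40 | 52 | 57.1, so 58 |
| d = 0.64, *n* = 39 (normal approximation) | 50.7, so 51 | 55.7, so 56 |
| d = 0.73, *n* = 31 | 40.3, so 41 | 44.3, so 45 |

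A one-sided test at d = 0.64 needs 31 completers and so also gives 41 or 45. One-sided at d = 0.73 needs 24 and gives 32 or 35. Among these variants, only d = 0.64, two-sided, multiplied by 1.3 reaches 51.

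**3. Completers left.** 51 × 0.7 = 35.7 per arm.

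**4. Power with what is left.**
- d = 0.64: noncentrality 0.64 × √(35.7/2) = 2.70, power 76.0% (75.2% with 35 per arm, 76.4% with 36).
- d = 0.73: noncentrality 0.73 × √(35.7/2) = 3.08, power 86.0%.
- Effect detectable with 80% power at 35.7 per arm: d = 0.67.

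**5. Dropout that 51 per arm can bear at d = 0.64.** Keeping 40 completers allows 51 − 40 = 11 losses, and 11/51 = 21.6%. Power is 81.5% at 20% dropout and 78.9% at 25%.

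**6. Size of the gap.** Division by 0.7 gives 57 to 58 per arm under the t test, which is 6 to 7 more per arm than 51.

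**The case against.** Four points can be made for the plan.

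**The main comparison may be adequately powered.** Section 2.6 puts the main analysis at 12 months. At d = 0.73 the retained sample has about 86% power, and even the correct allowance needs only 45 per arm. This stands, with one condition: section 2.2 says only follow-up, so applying 0.73 to the 12-month visit is an inference. A reader might infer from the dropout slip that the trial is underpowered for its main question, or that 102 patients are too few. The document does not support that.

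**The 30% may be loss by the end of the study.** Post-treatment is the first visit after an eight-week programme, so loss there could be lower, and at 20% the power at d = 0.64 exceeds 80%. This is possible, but it is an assumption. Section 2.2 applies a single rate to both effects, and its claim has to be judged on that rate.

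**The planned model is not a t test on completers.** Section 2.6 specifies intention-to-treat linear mixed models, and pain interference is measured at five visits. If the model gains from the baseline score with an assumed correlation *r* (d replaced by d/√(1 − *r*²)), 35.7 per arm gives 77.7% at *r* = 0.2, 79.8% at 0.3 and 82.9% at 0.4. Actual power could therefore be near or above 80%. The article states no such correlation, and its own calculation is a t test with dropouts counted as lost, so the stated derivation remains wrong.

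**The multiplication by 1.3 is not printed.** This also stands. A reader might take that mechanism as established, but it is inferred from the match to 51. The shortfall does not depend on it: however 51 was reached, losing 30% leaves 35.7 per arm.

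**Conclusion.** The concern holds in a limited form. On the paragraph's own t test and dropout rate, 51 per arm gives about 76% power at d = 0.64, four points below the stated 80%, and about 86% at d = 0.73. The result assumes a two-sided 5% test, 30% loss at the visit in question, and no information from patients who drop out.

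The error is modest. It affects the claim for the post-treatment effect and does not show a deficit in the 12-month main comparison, provided that 0.73 is the effect expected there. It should be corrected because the stated inputs and result disagree, but it does not threaten the trial's design.

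The abbreviation BDI in the same sentence is a clerical slip: the words beside it say pain interference, and the Abstract and the primary outcome section name the Brief Pain Inventory. It adds no weight to the point.

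**What to change.** Keep 102 patients and replace the closing claim in section 2.2 with wording such as: *51 per arm with 30% dropout leaves about 36 per arm, giving about 76% power for d = 0.64 at post-treatment and about 86% for d = 0.73 at follow-up.* In the same paragraph, change BDI to BPI.

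Do not add that the sample size was derived from d = 0.73. That effect leads to about 40 to 45 per arm, depending on the allowance and rounding, and so would misdescribe how 51 was reached.

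The cost is one sentence and a slightly less favourable power figure for post-treatment. No extra patients are needed and the analysis does not change.

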### 2.3. Procedure

The principal investigator ([name]), through an initial interview, will provide a general description of the study to patients with an indication for lumbar surgery interested in participating who met the eligibility criteria. Prior to random assignment to treatment (TAU or TAU + ACT), informed consent forms will be collected, which will include a general description of the characteristics of the interventions. Patients will also be informed that their participation will be voluntary and that they may withdraw at any time, with the guarantee that they will continue to receive their TAU. ACT will be performed by the psychiatrist ([name]) who is trained and accredited in ACT linked to the hospital’s Pain Unit, who has years of experience in individual and group management with this therapy at the level of patients with psychiatric comorbidity and chronic pain. The psychological intervention will be delivered before the participants have undergone surgery. At present, for our current protocol, in the context of the heterogeneity of the applications of perioperative psychological therapies in the studies published to date, it is not clear if patients who are candidates for surgery can benefit more from psychotherapeutic interventions in the preoperative period, in the postoperative period, or combined. In addition, the exact number of sessions and the adequate time to obtain improvement is unknown [56]. In our center, we have experience in patients with chronic pain with the 8-session ACT program. Given that the patients candidates for the study of our sample are a population at high risk of CPSP (i.e., already with preoperative pain) and considering the logistics that we can apply in our hospital (i.e., material and human resources), we find it interesting to study the response of 8 complete ACT therapy sessions in the preoperative period of this population and explore and share the findings.

This research will be carried out in accordance with the ethical standards established in the Declaration of Helsinki of 1964 and was approved by the Ethics Committee of the hospital (PR(ID) 2021/9998/I). Patient data will be treated confidentially, ensuring that only the research team can access this information after recoding the name and personal identity number. Only the principal investigator ([name]) will have access to the patient’s code key, which, in accordance with current data protection legislation in Spain, will be kept separately in a secure place. Participants will be assigned to the intervention group (TAU + ACT) or control group (TAU) using an SPSS v25 randomization list. Patients will be evaluated through 5 visits: 1 baseline visit (Visit 1), another visit after the ACT intervention (Visit 2), and other visits at 3, 6, and 12 months after surgery (Visits 3, 4, and 5). The RCT flowchart is presented in Figure 1.

